#### Economic evaluation

2.9.2

We will perform an economic evaluation from a societal and a health care perspective for quality‐adjusted life years, knee pain, and physical function. All patients included in the study will be analysed, with missing data handled by using multiple imputation by chained equations. Costs and effect differences will be estimated using seemingly unrelated regression analyses, in which their possible correlation can be accounted for. The 95% confidence intervals surrounding the cost differences will be estimated using bias‐corrected and accelerated bootstrapping. Subsequently, incremental cost‐effectiveness ratios will be estimated by dividing the differences in costs by the differences in effects. Uncertainty surrounding the incremental cost‐effectiveness ratios will be graphically illustrated by plotting BCA‐bootstrapped cost‐effect pairs on cost‐effectiveness planes. Also, cost‐effectiveness acceptability curves will be constructed to provide an indication of the probability of stratified exercise therapy being cost‐effective with usual care at different values of willingness to pay (Drummond, Sculpher, & Torrance, 2006).

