Upper leg muscle strength, assessed by the 30‐s chair stand test (30‐s CST). This performance test measures the maximum number of chair stand repetitions possible in a 30‐s period and is considered a measure of lower body strength as well as a performance‐based measure for physical functioning (Dobson et al., 2012)	X^a^	X^a^			X^b^
Body mass index (BMI): body weight (in kilograms) divided by squared body length (in metres)	X^a^	X^a^			X^b^
Waist circumference: distance around the abdomen in the horizontal plane midway between the lowest rib and the iliac crest (in centimetres; van Binsbergen et al., 2010)	X^a^	X^a^			X^b^

Economic evaluation					
Intervention‐related costs, assessed using a bottom‐up microcosting approach in which detailed data will be collected regarding the number and kinds of resources used as well as their respective unit prices (Goossens et al., 2000)	X	X	X	X	X
Other health care costs, including primary and secondary costs and prescribed medication, assessed using a cost questionnaire and valued in accordance with the Dutch Manual of Costing (Goossens et al., 2000)	X	X	X	X	X
Patient costs, including over‐the‐counter medication, informal care, and unpaid productivity costs, assessed using a cost questionnaire and valued using a recommended Dutch shadow price (Goossens et al., 2000)	X	X	X	X	X
Work‐related productivity costs, including patient‐reported productivity (work ability), and absenteeism (i.e., costs of being absent from work) and presenteeism costs (i.e., costs of being less productive while being at work), with costs valued using gender‐specific price weights (Goossens et al., 2000)	X^c^	X^c^	X^c^	X^c^	X^c^

Quality‐adjusted life years (QALYs), assessed by the EuroQol‐5D‐5L (EQ‐5D‐5L; 5 items), in which the patient can self‐rate their level of severity on five domains (mobility, self‐care, daily activities, pain/discomfort, and anxiety/depression; Kind, 1996). For the economic evaluation, the EQ‐5D‐5L health states will be converted into utility scores ranging from 0 (*death*) to 1 (*optimal health*) using the Dutch tariff (Hakkaart‐van Roijen, Van der Linden, Bouwmans, Kanters, & Tan, 2015; Kind, 1996). QALYs are calculated using the area under the curve approach	X	X	X		X
Process evaluation					
Number of sessions, registered by PT/dietician		X^d^			
Type of interventions per session, registered by PT/dietician		X^d^			

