### Sample size

2.8

According to the Cochrane review from Fransen et al. (2015), the average (between‐group) effect size (ES) of usual exercise therapy in knee OA on knee pain is 0.49, corresponding with a between‐group difference in mean improvement of 1.2 points (on 0–10 scale). In an RCT, comparable with our proposed study but in low back pain (Hill et al., 2011), stratified exercise therapy by a PT resulted in a (between‐group) ES of 0.3, compared with usual exercise therapy, corresponding with a between‐group difference in mean improvement of 0.5 points (on 0–10 scale). Based on a mean improvement 1.2 points (on 0–10 scale) for usual exercise therapy, our experimental intervention should result in a mean improvement of 1.7 points (on 0–10 scale). As this is lower than the mean improvement of 2.1 points found in our uncontrolled pilot study (*n* = 50; Knoop et al., 2019), this effect is highly plausible. With an expected between‐group difference in mean improvement of 0.5 points (on 0–10 scale), an estimated standard deviation of 1.4, α = .05 (two‐sided testing), power = 90%, design effect of 1.05 (with an estimated mean number of patients per cluster [i.e., PT practice] of 6), and 15% dropout rate, 408 patients (204 per group) will be needed.

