#### Effectiveness evaluation

2.9.1

All patients included in the study will be analysed, with missing data from withdrawals handled by maximum likelihood estimation (“dealing with missing values”). Statistical significance will be accepted at *p* values of less than .05 (two‐sided testing). Baseline patient and PT characteristics in both study groups will be presented using descriptive statistics (mean/standard deviation, median/range, or proportions) to check similarity between arms. Descriptive statistics comparing both study groups will also be calculated for other study parameters (e.g., costs and process parameters). The primary analysis will be an intention‐to‐treat, multilevel, regression analysis comparing stratified versus usual care for the primary outcome measures, with 3‐month follow‐up as a primary time‐point and 6‐ and 12‐month follow‐up as secondary time‐points. In this analysis, we will take into account the level of PT practice, level of patient, and level of time‐point. In addition, we will perform a post hoc analysis with an additional level of PT, with the appropriateness of this additional level tested using the −log 2 likelihood test. Furthermore, we will perform a post hoc analysis comparing stratified versus usual care but now separately for each of the three subgroups. Only if deemed necessary, the analysis should be adjusted for important prognostic characteristics that potentially confound the treatment effects (e.g., pain severity, duration of symptoms, upper leg muscle strength, and BMI) or for important baseline patient characteristics (e.g., outcome measure) or PT characteristics that substantially differ between the two arms. We will perform similar analyses for secondary outcomes measures, except for GPE, which is analysed as a dichotomous variable (“completely recovered” and “much recovered” vs. all other responses), using logistic multilevel analysis.

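### The economic evaluation names methods that handle only the cost-effect correlation, not practice clustering; done at patient level, they would overstate precision, modestly at the plan's own ICC

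*Protocol article*

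**What the plan says.** The trial randomises physical therapy practices: 55 were recruited and allocated 1:2 to experimental and control, with 204 patients planned in each arm (Section 2.5).

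For the clinical outcomes, Section 2.9.1 states "we will take into account the level of PT practice, level of patient", with time-point as a further level. The sample size (Section 2.8) also allows for clustering, with a "design effect of 1.05" at a mean of 6 patients per practice.

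For the economic evaluation, Section 2.9.2 covers QALYs, knee pain and physical function. Its estimator is given as follows: "Costs and effect differences will be estimated using seemingly unrelated regression analyses, in which their possible correlation can be accounted for". On uncertainty it says "The 95% confidence intervals surrounding the cost differences will be estimated using" BCa bootstrapping, and the bootstrapped cost-effect pairs are then plotted on cost-effectiveness planes. Missing data are imputed by chained equations. The section names no practice level, resampling unit, cluster-robust variance or covariate.

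Table 2 lists the EQ-5D-5L at 0, 3, 6 and 12 months and costs from baseline onwards, and states that "QALYs are calculated using the area under the curve approach".

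**The concern.** Two sections treat the same trial differently. Pain and function are modelled with a practice level in 2.9.1. They reappear as effects in 2.9.2 under methods for which the only stated dependence is that between a patient's costs and effects. Seemingly unrelated regression (SUR), the BCa bootstrap and chained equations, each used in its usual form, take patients as independent. Someone following 2.9.2 literally could resample and impute patients without regard to practice.

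Cost-effectiveness is part of the trial's stated hypothesis. Whenever the ICC is positive, leaving out practice errs in one direction: cost intervals too short, the cloud on the plane too tight and the acceptability curve too steep.

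A secondary matter is baseline utility. It enters the area-under-the-curve QALY directly and usually also predicts later utility. Section 2.9.1 allows conditional adjustment for the baseline outcome; 2.9.2 mentions no adjustment.

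**Working it through.** **1. The plan's own sample size.** The inputs from Section 2.8 are a "difference in mean improvement of 0.5 points (on 0–10 scale), an estimated standard deviation of 1.4", two-sided α of 0.05, 90% power, design effect 1.05 and 15% dropout.

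- Per arm: 2 × (1.4 × (1.960 + 1.282) / 0.5)² = 164.8, rounded up to 165.
- Times the design effect: 165 × 1.05 = 173.25.
- Allowing for dropout: 173.25 / 0.85 = 203.8, rounded up to 204 per arm, 408 in total.

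The stated 408 is reproduced. Without the design effect the total would be 390, so clustering accounts for 18 patients.

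**2. Implied ICC.** Design effect = 1 + (m − 1) × ICC. With 1.05 and m = 6, ICC = 0.05 / 5 = 0.01. This is for the pain outcome. None is given for costs or QALYs.

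**3. Patients per practice by arm.** A 1:2 split of 55 practices gives about 18.3 and 36.7. With 204 patients per arm that is 204 / 18.33 = 11.1 (experimental) and 204 / 36.67 = 5.6 (control).

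**4. Effect of ignoring practice.** With equal patient numbers per arm, the variance inflation of the difference is the mean of the two arms' design effects (DE). A patient-level interval is too narrow by 1 − 1/√DE. Its coverage is about 2Φ(1.96/√DE) − 1, a normal approximation.

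| ICC | DE experimental | DE control | Mean DE | Too narrow by | Coverage of nominal 95% |
|---|---|---|---|---|---|
| 0.01 (implied by Section 2.8) | 1.101 | 1.046 | 1.073 | 3.5% | 94.1% |
| 0.02 (assumed) | 1.203 | 1.091 | 1.147 | 6.6% | 93.3% |
| 0.05 (assumed) | 1.506 | 1.228 | 1.367 | 14.5% | 90.6% |
| 0.10 (assumed) | 2.013 | 1.456 | 1.735 | 24.1% | 86.3% |

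At the plan's design effect of 1.05 exactly, the interval is 2.4% too narrow and coverage is 94.4%. With 15% dropout (9.5 and 4.7 patients per practice), the figures are 2.9% at ICC 0.01, 12.5% at 0.05 and 21.2% at 0.10. The formula assumes equal practice sizes within an arm.

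**5. Weight of baseline utility in the QALY.** Trapezoids over 0, 3, 6 and 12 months give weights of 0.125, 0.25, 0.375 and 0.25, which sum to 1. A baseline difference d, of which a fraction s carries through to every later visit, shifts the unadjusted QALY difference by d × (0.125 + 0.875 × s). The documents give neither d nor s. As an illustration:

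| Assumed d | s = 0 | s = 0.5 | s = 1 |
|---|---|---|---|
| 0.01 | 0.0013 | 0.0056 | 0.01 |
| 0.02 | 0.0025 | 0.011 | 0.02 |
| 0.05 | 0.0063 | 0.028 | 0.05 |

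**The case against.** The strongest reply is that 2.9.2 does not exclude clustering. SUR accepts cluster-robust variance and covariates in each equation, a BCa bootstrap can resample practices, and chained equations can include practice. The article is a condensed account, and it points to a fuller research protocol in the trial register and on the Open Science Framework, which is not shown here. The resampling unit and the covariate list are often set out there. This part of the reply stands. A reader might infer that the analysis is single-level and that its intervals are therefore too narrow, but the text says neither.

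The reply does not remove the point. Section 2.9.2 is specific about estimator, interval method and imputation, and it names one dependence to be handled. The practice level that 2.9.1 gives to the same pain and function outcomes is absent.

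A second reply is that the effect is small at the only ICC the article implies. That also stands. Whether costs cluster more than pain is open. Control practices continue their previous habits, and each experimental practice has its own collaborating dietician, which suggests more clustering. Against that, experimental session numbers are set by patient subgroup within ranges, and total costs include other health care, patient and productivity costs that practices do not directly determine.

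A third reply concerns baseline utility: chance imbalance under randomisation is imprecision, not bias, and silence on covariates alone is not a fault in an article. This is correct. A reader might infer that the QALY difference will be biased, but the documents show no imbalance. What remains is that unblinded therapists screen patients after their practices were allocated, so a systematic imbalance is possible. That is one reason to adjust, together with the gain in precision.

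**Conclusion.** The point holds as a should-fix. The economic methods are specified for a practice-randomised trial without the practice level used for the clinical outcomes. Carried out in standard patient-level form, they would overstate precision in the cost intervals, planes and acceptability curves.

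The size depends on an ICC that the article does not give for costs or QALYs. It is about 2.4% to 3.5% of interval width, with coverage about 94%, at the implied ICC of 0.01. It reaches 14.5% to 24.1%, with coverage 90.6% to 86.3%, only at assumed ICCs of 0.05 to 0.10. These figures rest on equal practice sizes within arm and a normal approximation.

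Adjusting for baseline utility and costs is a supporting recommendation. The utility shifts shown are illustrations under assumed imbalances, not estimates of bias in this trial.

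**What to change.** State in Section 2.9.2 that costs and effects are analysed with allowance for practice, consistent with 2.9.1:

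- Fit SUR with practice-level cluster-robust variance, or a bivariate multilevel model. Either is acceptable.
- Draw bootstrap samples by resampling practices within arm, and use the same samples for the intervals, the planes and the acceptability curves.
- Include practice in the imputation model.
- Put baseline EQ-5D utility in the QALY equation and baseline costs in the cost equation. Both are already collected at t0. This usually improves precision and removes the part of any imbalance that the measured baseline explains, including imbalance arising from unblinded recruitment after allocation.

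If the unseen full protocol already says this, one sentence in 2.9.2 is enough. Otherwise the cost is wording and some programming, with no new data. Allowing for practice makes the intervals slightly wider if the ICC is near 0.01 and more so if costs cluster more strongly.

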#### Process evaluation

2.9.3

We will analyse all process parameters descriptively, in which treatment arms will be compared. In addition, qualitative information from the interviews will be analysed descriptively.

### Timelines

2.10

Recruitment and training of PTs occurred between June and December 2018. Ethics approval was obtained at the VU University Medical Center in January 2019. Start of the trial and patient inclusion occurred after this approval.

The anticipated timeline for the CRCT is as follows:
January 2019Start of inclusion and data collectionFebruary 2020Inclusion completedMay 2020All participants completed t3 (immediate post‐treatment)February 2021End of data collection: All participants completed t12

## DISCUSSION

3

OA is one of the most disabling diseases, costing globally more than 150 billion dollar each year (Ma, Chan, & Carruthers, 2014). Exercise therapy is recommended as a first step treatment option for patients with knee OA in all relevant clinical guidelines. We hypothesize that with our model of stratified care, PTs will be able to optimize their knee OA treatment in a cost‐effective manner. In addition, dieticians may also be able to optimize their treatment in obese patients with knee OA by using our model and collaborating more strongly with the PT. The stratified care model, tested in the undergoing trial, was developed on the basis of our previous research on optimization of exercise therapy effects (de Rooij et al., 2017; Edelaar et al., 2017; Knoop et al., 2013; Knoop et al., 2014; Knoop et al., 2015) and clinical phenotypes (Knoop et al., 2011; van der Esch et al., 2015) and was found to be feasible in a primary care setting (Knoop et al., 2019). Phenotyping and stratified care are considered the “holy grail” in medical research (Foster, Hill, O'Sullivan, & Hancock, 2013). For stratified care development, different approaches can be used: a prognostic risk approach, a responsiveness to treatment approach, or a aetiological/mechanistic approach (Foster et al., 2013). In contrast to the well‐known model of stratified care in low back pain that was based on the first approach (using the STarT Back Screening Tool, Hill et al., 2011), our stratified care model had been developed from a clinical perspective using a combination of the second and third approach. It has thereby the potential to optimize (cost‐)effectiveness of exercise therapy for a very large and strongly increasing patient group. Even more important, due to the simplicity of the stratification algorithm, our model, if proven to be (cost‐)effective, can easily be implemented in daily practice and quickly adopted in current guidelines, similar as for the STarT Back Screening Tool (de Campos, 2017).

Our study design has several other strengths. First, this trial will be conducted in a primary care setting in “real‐world” patients in a large number of patients and PTs, so our findings can be expected to be representative for daily practice. Second, our intervention has already been found to be feasible in primary care with promising results on outcome measures but had been further improved on the basis of the study findings from our pilot study (Knoop et al., 2019). Therefore, it is unlikely that we will face feasibility issues during our trial. Third, our sample size has been calculated to detect minimal clinically important differences between groups and also enable us to perform explorative, secondary analyses to compare both interventions within each subgroup. Fourth, we added a dietary intervention to our subgroup‐specific exercise therapy intervention for the obesity subgroup. This interdisciplinary approach is not provided in usual care and can be expected to optimize current treatment effects in this complex and increasing patient group. Fifth, our outcome measures cover a broad spectrum of clinical and economic constructs, whereas we also collect detailed (quantitative and qualitative) information on treatment content, fidelity, and adherence. Thereby, the OCTOPuS study will gain new insights how to further optimize exercise therapy for patients with knee OA.

## IMPLICATIONS FOR PHYSIOTHERAPY PRACTICE

4

Exercise therapy is recommended as a first step treatment option for patients with knee OA in all relevant clinical guidelines, but current clinical effects are modest and should be further optimized. A stratified approach to exercise therapy, whereby patients are allocated to homogeneous subgroups and receive a stratified, subgroup‐specific intervention, can be expected to optimize current clinical effects. This new approach, which was found to be feasible with promising effects in a pilot study, is currently being tested for its effectiveness and cost‐effectiveness compared with usual best practice by PTs in in a CRCT (OCTOPuS study). If proven to be (cost‐)effective, this intervention can easily be implemented in daily practice and quickly adopted in current guidelines.

## ETHICS APPROVAL AND CONSENT TO PARTICIPATE

This study has been approved by the Medical Ethical Committee of the VU University Medical Centre (2018.563). We conduct this study in agreement with the Declaration of Helsinki (2013), in accordance with the Dutch Medical Research Involving Human Subjects Act (WMO) and the General Data Protection Regulation (in Dutch: Algemene Verordening Gegevensbescherming, AVG). We obtain written informed consent from each subject, after the information letter has been provided. The researchers make sure that the participants are given complete, adequate, written, and oral information regarding the nature, aims, possible risks, and benefits of the study. We explain to the participants that they are free to interrupt their participation in the study at any moment without any consequence and that they are able to receive a digital copy of their personal data. Participants should keep a copy of the information sheet and informed consent form. An independent expert has been appointed to provide subjects the opportunity to ask questions about the study to someone not related to the study.

## AVAILABILITY OF DATA AND MATERIALS

The datasets generated and/or analysed during the current study will be available in the Dataverse repository (https://dataverse.nl/dataverse/BETA). The research protocol is accessible at the Netherlands National Trial Register (https://www.trialregister.nl/trial/7463) and Open Science Framework (https://osf.io/x3p94/).

## TRIAL REGISTRATION

The Netherlands National Trial Register (NTR): NL7463 (date of registration: January 8, 2019).

